## Abstract

**Introduction:**

Administration of spinal cord stimulation to individuals with PSPS-T1/2 may induce supraspinal descending activation. Similarly, exercise is recognized as a fundamental aspect of spinal pain management. Studies have demonstrated its impact on neurophysiological factors, including the release of spinal and supraspinal beta-endorphins, which activate μ-opioid receptors. Therefore, the purpose of this study will be to examine the effect of SCS in combination with lumbo-pelvic stability core training on perceived low back pain, quality of life and disability in PSPS-T2 patients.

**Methods/Materials:**

A double-blind randomized clinical trial (RCT) has been designed. All participants will be randomized from a pre-set sequence. The intervention design has been elaborated from the CONSORT guidelines. This study has been registered at Clinicaltrial.gov (NCT06272539). Sample size was calculated using G Power® Sample size software (University of Düsseldorf). The calculation was based on a moderate effect size of 0.7 (partial η2 = 0.70, α = .05, power = 0.95), resulting in a total of 40 patients. Assuming a 30% dropout rate, 52 participants will be recruited in total. Two sessions per week will be scheduled for 8 weeks with a total of 16 sessions. Each work session will have a duration of 60 minutes. The exercise will be adapted according to the phases based on the results already published, limiting in each phase the degrees of flexion and extension of the spine to avoid the risk of electrode migration. Primary outcomes will be functionality, satisfaction, strength, psychosocial variables, quality of life and pain perception.

## 1. Background

Chronic spinal pain is characterized by persistent pain that is not always accompanied by structural abnormalities, leading to a discordance between the two [1]. A common clinical presentation of this type of pain is failed back surgery syndrome (FBSS) [2]. However, diagnostic labels for this condition have been considered inadequate, misleading, and potentially troublesome [3]. As an alternative, the term persistent spinal pain syndrome (PSPS) [4] has gained interest due to its high prevalence and recurrence in the clinical practice of pain management specialists [5]. Consequently, new nomenclature, PSPS-T1 and -T2, is now routinely used in publications [6]. The primary symptoms of chronic spinal pain include lower back pain, severe disability, poor quality of life, and high unemployment rates [7]. Additionally, the heterogeneity of these patients complicates diagnosis and evaluates the clinical effect of each treatment modality [8]. This may be due to the existence of peripheral and central mechanisms that trigger the state of the central nervous system [9].

The PSPS-T2 condition has the potential to affect a substantial number of people in the general population, with several factors related to the nervous system’s neuroplasticity. The progression and adaptation of the condition may be influenced by biological diversity, as well as psychological and social factors [10]. To aid in muscle recovery during rehabilitation, advanced treatments, including the use of neuromodulatory strategies, are employed [11]. Therapeutic approaches for PSPS-T2 vary and include surgical reintervention, pharmacological treatments, and more conservative methods that focus on exercise and behavioral therapies [12,13]. Spinal cord stimulation (SCS) is one such intervention, with a medium-term effect that can last up to 2 or 3 years [14] although several studies suggest that long-term outcomes are favourable with regard to pain relief among individuals with predominant radicular pain [15]. SCS has been shown to alleviate pain and reduce analgesic consumption, and improve quality of life [16]. However, the programming of SCS may modify glial signaling through the modulation of neuronal and glial cell activation in patients, and the effects of SCS on patients with persistent spinal syndrome are yet to be determined [17]. Nevertheless, the conditioned modulation of pain may be associated with the effect of SCS [18].

In terms of published findings, there is a remarkably low quality for the majority of the use of SCS for treating persistent pain [19]. The intricacy of pain necessitates healthcare professionals to propose a multidisciplinary approach [20]. To this end, a patient-centered approach has recently been regarded as a crucial component for individuals with persistent pain [21]. Exercise therapy, in particular, is considered the fundamental aspect of spinal pain treatment [22]. Research indicates that motor control and spinal stabilization exercises, as opposed to surgical and pharmacological interventions, are more effective in reducing pain and disability for patients with spinal pain [23,24]. Recent observations have emphasized the significance of muscle inhibition as a trigger for loss of function and pain in patients with chronic low back pain [25]. In addition to its biomechanical effects, exercise treatment is an intervention that supports self-management of care [26] by reinforcing the utilization of strategies to enhance biopsychosocial beliefs [27].

The application of integrated interventions may lead to enhanced results in both the short-term and medium-term periods [28]. Combining SCS therapy with physical exercise may not only improve outcomes, but it may also result in a higher number of patients experiencing sustained benefits. However, it is important to consider the potential adverse events that may occur when implementing spinal cord stimulation (SCS) and exercise together, such as electrode migration. Approximately one in ten patients who receive SCS implants experience lead migration [29]. Additionally, the high incidence of lead displacements (3.07%) should not be overlooked [30]. According to the postoperative treatment guidelines, patients are advised to refrain from engaging in any form of exercise or assuming positions that involve the end range of motion in the lumbar spine for a period of two months following the operation. This precautionary measure is necessary as it can potentially result in the migration of the implanted electrode. It is essential to allow sufficient time for the surrounding tissues to undergo fibrosis and securely anchor the electrode in place. Patients with PSPS T2 may have protective attitudes influenced by fear of pain due to movement (kinesiophobia), which can exacerbate patient deconditioning [31]. Therefore, treatment should focus on enhancing the patient’s perceptions and beliefs about movement and addressing not only mechanical and functional parameters but also improving the overall experience [32]. The use of both treatment techniques (SCS/exercise) has resulted in moderate-quality evidence, presenting low-effect measurements when applied in isolation [33]. Furthermore, implementing an exercise protocol that minimizes the risk of adverse effects is crucial. Designing an exercise program based on the range of motion of the spine may be particularly beneficial in avoiding adverse effects on SCS. This study aimed to evaluate the effect of combined treatment with SCS and exercise focused on neuromuscular control of CORE in comparison with isolated treatment with SCS on functionality, pain perception, psychosocial variables, patient satisfaction, adverse effects, and quality of life in patients diagnosed with PSPS-T2. Based on these recommendations, the hypothesis proposed in this study aimed to capitalize on the analgesic effect of posterior cord stimulation during a window of opportunity while the patient underwent re-education through neuromuscular and core control exercises. The integration of these two treatment techniques is expected to yield superior effects compared to the application of a single treatment in isolation.

## 2. Materials and methods

### 2.1 Study design

This study was designed as a simple-blinded, comparative longitudinal, and prospective randomized controlled trial (RCT). The protocol was written according to the SPIRIT statement, increasing its transparency and completeness (Fig 1) [34]. The findings will be reported following the TIDieR checklist [35].

**Fig 1 pone.0309935.g001:**
[figure not shown]
Execution schedule–recruitment, intervention, and reassessment.

This study will be a research protocol for two groups: SCS and core and control motor exercises with an allocation ratio of 1:1. Data will be collected from April 2024 to January 2026. All participants will sign an informed consent form, prepared in accordance with the ethical guidelines of the Helsinki Declaration [29]. The study protocol was approved by the Ethics Committee on January 24, 2024 (ID: 2023 10 1435). This study was prospectively registered in the Clinical Trials (Registration number: NCT06272539) (Supplementary file 1)

### 2.2 Informed consent

After assessing the patient and obtaining pertinent information, individuals who willingly express their interest in participating in the study and have signed the necessary informed consent forms will be chosen based on predetermined eligibility criteria. These selected participants will then be randomly assigned.

### 2.3 Study population

The participants will be patients diagnosed with spinal pain syndrome who are undergoing SCS at the Pain Unit at the Hospital of Salamanca. The participants will be selected according to the compliance criteria established by the criteria established by the guidance Neurostimulation Appropriateness Consensus Committee (NACC) of neurostimulation practice [36]. All patients will be informed of all the study procedures, and those of interest will be provided with a brief introduction to the selection process.

### 2.4 Inclusion and exclusion criteria

The eligibility inclusion criteria will be as follows: diagnosis of PSPS-T2 with leg and back pain; ii) patients older than 18 years; iii) ≥6 months with pain and iv) VAS score >7. Exclusion criteria were: (i) previous surgeries in the abdominal area, (ii) pregnancy or lactation, (iii) severe fractures or pathologies, (iv) spinal structural deformity, and (vi) neurologic or psychiatric issues.

### 2.5 Procedure

Once the groups have been established, there will be six sample collections: Pre, Post3weeks, Post2months, Post6months, Post12months and Post18months (Fig 2). Patients will be introduced to the CORE neuromuscular and control motor exercise protocol after surgery.

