## 3. Randomization and blinding

By doing so, we aim to eliminate or reduce potential biases due to the order of patients and any transference effects that might occur if one profile clinical patient will influence the performance in several evaluations. All individuals in the treatment cohort will be overseen by two physiotherapists with extensive experience (>10 years). One physiotherapist will administer the interventions for all two groups, while the other will perform the evaluations, ensuring that the second physiotherapist remains blinded to the evaluated group. An unbiased outcome ascertainment will be ensured by an independent researcher who will create a table of random numbers using an Excel formula to blind data collectors and outcome adjudicators. A block randomization design with block sizes of 4 or 8 will be applied to ensure equal distribution of participants across each group. The randomization sequence will be secured on a USB drive and stored under lock and key by an independent researcher, accessible only when necessary. A single-blind design will be employed due to the impossibility of blinded participants and the treating physiotherapist for exercise intervention. Specifically, each patient will complete a sequence of allocation in the order of A, B, B, A, where ’A’ represents SCS treatment isolated, and ’B’ denotes combined treatment. Subsequently, the average of the two ’A’ conditions was calculated, and the same process was applied for the ’B’ conditions.

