## 5. Patient-reported outcome measures

### 5.1 Primary outcomes

#### 5.1.1 Disability. Oswestry disability index

The Oswestry disability index (ODI) is the most widely used and validated assessment test for lumbar pain. It is a self-assessment test divided into ten sections designed to assess limitations in daily life. Each section has a score ranging from 0 to 5, where 5 was the highest instability level, with the maximum possible score being 50 points [39]. The total rate will be calculated by dividing the participant’s score by the maximum possible score and dividing it by 100 to obtain a percentage [40]. A higher score on the questionnaire indicates greater disability associated with low back pain [41]. ODI is widely regarded as the “gold standard” among tools for assessing functional outcomes in low back conditions [42]. The ODI index is validated to Spanish [43] presenting high sensitivity and specificity to evaluate the function [44,45].

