#### 8.2.2 Analysis of the outcome measures

Following the Consolidated Standards of Reporting Trials (CONSORT) guidelines on the reporting of RCTs, a per-protocol analysis will be performed. The normality assumption will be checked with the Kolmogorov–Smirnov test and box-plot analysis, while the homogeneity of the variance will be tested through the Levene test. To analyze the acute and short-term effects of SCS and SCS combined with core and control motor exercise on PSPS T2, a two-way ANOVA for repeated measures with experimental groups (i.e., Post3weeks, Post2months, Post6months) as factors will be used, followed by Tukey corrections, to examine time, group, and interaction effects through within- and between-group comparisons (primary and secondary outcomes). The results will be presented as the mean difference (MD) and confidence interval at 95% (IC95%). Effect size (ES) will be estimated by calculating Cohen’s d coefficient. All analyses will be performed using the statistical analysis software SPSS 24 (IBM Inc., Chicago, Illinois, USA). In the case of dropouts during the study or if the statistical power is less than the established 80%, an intention-to-treat principle analysis will be performed [71]. The normality of the data will be tested by visual inspection of histograms, and the characteristics of the participants will be presented using descriptive statistical tests. To assess between-group differences in response to treatment at each post-baseline time point, the mean between-group differences and their associated 95% confidence intervals (CI) will be calculated by constructing mixed linear models using interaction terms (group vs. time). The treatment effects will be adjusted by including baseline outcome values as covariates in the model. Statistical analysis will be conducted by a researcher who is not involved in any of the phases of data collection and will receive data in coded form. Minimal clinically important differences are patient-derived scores that reflect changes in a clinical intervention that are meaningful to the patient. To do this from the delta percentage (Δ%) will calculate using the standard formula: change (%) = [(post-test score − pre-test score)/pre-test score] × 100.

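### As worded, Section 2.5 puts the Pre assessment after group formation, so a self-reported baseline used in the analysis could be influenced by knowledge of the arm

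*Protocol article*

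**What the plan says.** Section 2.5 sets the measurement schedule: "Once the groups have been established, there will be six sample collections: Pre, Post3weeks, Post2months, Post6months, Post12months and Post18months". Pre is the first of six collections, and all six follow the formation of the groups. The sentence refers to Fig 2, which is not shown.

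Section 2.2 describes what comes before assignment. It begins "After assessing the patient and obtaining pertinent information, individuals who willingly express their interest in participating in the study", goes on to signed consent and the eligibility criteria, and ends "These selected participants will then be randomly assigned". It does not say what the assessment contains and does not call it Pre.

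On blinding, Section 3 states: "A single-blind design will be employed due to the impossibility of blinded participants and the treating physiotherapist for exercise intervention". The evaluating physiotherapist is a different person, with the arrangement "ensuring that the second physiotherapist remains blinded to the evaluated group". The abstract calls the trial double-blind, but Sections 2.1 and 3 describe single blinding and Section 3 gives the reason.

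Section 5.1.1 says of the ODI, the primary outcome: "It is a self-assessment test divided into ten sections designed to assess limitations in daily life". The pain VAS is the patient's own mark (Section 5.2.2), and the Tampa and catastrophizing scales are self-administered (Sections 5.3.2 and 5.3.4).

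Section 8.2.2 says of the mixed linear model: "The treatment effects will be adjusted by including baseline outcome values as covariates in the model". The same section defines percent change with the pre-test score both subtracted and used as the denominator.

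**The concern.** Baseline adjustment is safe in a randomised trial because the covariate is fixed before treatment is assigned, so assignment cannot move it. A questionnaire completed by a patient who already knows the arm loses that guarantee. Someone told they will get stimulation alone may report more disability out of disappointment; someone told they will get the exercise programme may report less, in anticipation. Blinding the evaluator does not help, because for these instruments the patient is the rater. Keeping the randomisation sequence under lock protects the assignment itself, not a score recorded afterwards.

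What is at stake is the adjusted between-group difference in Section 8.2.2 and the percent change used there for clinical importance. The baseline comparison in Section 8.2.1 would be affected too: a difference at Pre could no longer be read as chance imbalance.

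**Working it through.** The point concerns the order of steps, so there is no figure in the plan to reproduce. The check has two parts.

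**1. The order, read across sections**

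- Section 2.2: assessment of unspecified content, consent, eligibility, then random assignment.
- Section 2.4: eligibility requires a VAS above 7, so a pain score must exist before assignment. No criterion uses the ODI.
- Section 2.5: groups established, then Pre and the five post visits.
- Section 3: participants unblinded, evaluator blinded. No statement on when the patient is told the arm.

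Read together, these give eligibility, randomisation, Pre. Nothing identifies the Section 2.2 assessment as the Pre collection, and nothing delays disclosure until Pre is done.

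**2. Possible size (illustration)**

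Inputs from the document: planning difference 1.95, SD 3.2 and 20 evaluable patients per group (Section 4). Section 4 ties these to disability without giving the scale unit, so *points* below means the unit of those figures. Assumed, because the document gives neither: the allocation-induced shift s in reported baseline (exercise arm minus control arm) and the baseline slope b. With equal variances at baseline and follow-up, b equals the correlation between them. The shift is taken to affect Pre only, not follow-up.

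The adjusted effect is (difference in follow-up means) - b × (difference in baseline means). Adding s to the baseline difference changes it by

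bias = -b × s, and for a simple change score, bias = -s.

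| Shift s | Adjusted bias, magnitude, b = 0.3 to 0.7 | As % of 1.95 | Change-score bias as % of 1.95 |
|---|---|---|---|
| 0.25 | 0.075 to 0.175 | 3.8 to 9.0 | 12.8 |
| 0.5 | 0.15 to 0.35 | 7.7 to 17.9 | 25.6 |
| 1.0 | 0.30 to 0.70 | 15.4 to 35.9 | 51.3 |

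For example, 0.3 × 1.0 = 0.30 and 0.30 / 1.95 = 15.4%; 0.7 × 1.0 = 0.70 and 0.70 / 1.95 = 35.9%.

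Direction: higher ODI is worse, so a beneficial exercise effect is negative. If the control arm reports a worse Pre score, or the exercise arm a better one, s is negative and the bias is positive, against exercise. If the exercise arm reports a worse Pre score, the bias favours exercise.

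Type I error was simulated for a baseline-adjusted comparison at one follow-up (SD 3.2, assumed correlation 0.5, 20 per arm, no true effect, 4000 runs). It was 0.049 with no shift, 0.065 with a 0.5-point shift and 0.082 with a 1-point shift.

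**The case against.** The strongest reply is that one loosely worded clause carries the point. Its sentence refers to Fig 2, captioned as the randomisation flow chart and measurement protocol, and Fig 1 is the execution schedule. Neither is shown, and either could place Pre before randomisation. Section 2.2 does put some patient assessment before assignment, and the VAS criterion means at least one pain score exists by then. A journal article may also leave visit-level timing to the full protocol.

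Much of this stands and limits the point. It does not remove it. The article states an order instead of leaving it open, and that order is the less favourable one. The pre-assignment assessment is not identified as Pre, and the VAS criterion does not cover the ODI. If the figures show the safer order, the text needs correcting to match; if they do not, the procedure needs changing.

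Stronger readings are tempting and should be resisted:

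- A reader might infer that patients know their arm when they complete Pre. No section says so; forming the groups is not the same as telling patients.
- A reader might infer that the baseline is unblinded throughout. The evaluator is blinded; only the patient's self-report is exposed.
- A reader might assume a large shift. Three points, for instance, would be 3 / 3.2 = 0.94 of the planning SD, and nothing in the document supports it. The smaller shifts used above are assumptions as well.
- A reader might apply the change-score column to the main estimate. Section 8.2.2 plans a baseline-adjusted mixed model, and the repeated-measures ANOVA there names only post-baseline time points. The full shift would enter only where a raw change is compared; percent change also has Pre in its denominator.

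**Conclusion.** The point holds as a risk created by the stated order, not as a demonstrated bias. Section 2.5 places Pre after group formation, Section 2.2 does not identify an earlier outcome baseline, and no text withholds allocation until Pre is complete. With unblinded patients and self-reported outcomes, the baseline could be influenced by allocation, and it enters both the adjusted model and the percent change.

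The size cannot be determined from the document. Under the assumptions stated, a 1-point differential shift would bias the adjusted effect by 0.3 to 0.7 points in magnitude, roughly 15% to 36% of the planning difference, in a direction set by which arm shifts. If patients do not learn their arm before Pre, the bias from this source is zero. The conclusion is conditional on Figs 1 and 2, which could settle the order. The correction is still worth making, because it removes a possible bias at almost no cost.

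**What to change.** Reword Section 2.5, consistently with Section 2.2 and Figs 1 and 2, to say that the Pre assessment of all outcomes is completed and recorded before the allocation is drawn, or at the latest before it is disclosed to the patient or the treating physiotherapist. State that only the five post visits follow assignment. If the Section 2.2 assessment is in fact the Pre collection, name it as such and list the instruments completed there, including the ODI.

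No visits, patients or measurements are added; the only cost is the ordering of steps. If patients have already been enrolled under the current wording, record for each whether Pre preceded disclosure, so that the report can say so.
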